## **14-2. Number of patients planned and rationale**

Target sample size 484

The rationale for setting the target number of patients :

The primary endpoints of this study were the rates of intraoperative thrombotic morbidity and symptomatic ischemic pathology on MRI-DWI (IRC). Rie et al reported^12^ a total of 8.8% incidence of thromboembolism in 159 patients with cerebral aneurysms who received intraoperative antiplatelet therapy and 17.6% in 102 patients who did not. In addition, at our institution and relevant institutions, based on the imaging findings obtained on MRI DWI on the day after the operation, in 27 patients who underwent endovascular aneurysm embolization for cerebral aneurysms, 14.8% (4 of 27 patients) showed ischemic lesion 15 mm or higher.

Therefore, the incidence of intraoperative thrombotic complications in the placebo-treated group and the incidence of symptomatic ischemic disease on MRI-DWI were assumed to be 15%. Assuming that aspirin treatment improves both by 10%, we assumed that the incidence of intraoperative thrombotic morbidity in the aspirin group and the incidence of symptomatic ischemic pathology on MRI-DWI would be 5% each. Under these assumptions, a two-sided significance level of 2.5% would result in a sample size of 460 patients (230 patients in each group), requiring 90% power for each intergroup comparison of the endpoints. The target sample size was 484 patients (242 in each group) with a dropout rate of approximately 5%.

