## **14-3. Statistical analysis**

**Analysis of the primary endpoint**

1) Incidence of intraoperative thrombotic complications

2) Incidence of symptomatic ischemic involvement in MRI-DWI (IRC).

The superiority of the aspirin-treated group to the placebo-treated group will be tested in mITT using Cochran-Mantel-Haenszel (CMH test stratified by age (≧65 years, <65 years), sex (men, women), WFNS grade (I-III, IV-V), and modified Fisher grade (0-2, 3-4. Considering the multiplicity of tests, the two-sided significance level in the comparison between the groups for each endpoint was 2.5 %. The number and percentage of patients with events were calculated for each group, and the difference in the percentages between the two groups (aspirin group vs. placebo group) was calculated with a 97.5% confidence interval.

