**Analysis of the key secondary endpoints**

1) Incidence of all bleeding events within 14 days of onset

2) Incidence of global cerebral ischemic events in the first 14 days after MRI radiography after surgery

For mITT, the number and percentage of patients with events will be calculated in each group, and the difference in the percentage between the two groups (aspirin-placebo group) and the 95% confidence interval will be calculated. If the upper limit of the confidence interval was less than 10%, non-inferiority was demonstrated. Comparisons between the groups for each endpoint will be based on the closed test procedure described above.

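### The key secondary non-inferiority claims rest on a closed test procedure that the protocol never describes, so familywise error control over primaries and key secondaries cannot be established

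*Protocol*

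**What the plan says.** The protocol calls the trial confirmatory and has two primary endpoints: intraoperative thromboembolic complications, and symptomatic ischemic lesions on DWI as judged by the independent committee. Three parts of section 14 bear on multiplicity.

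- **Primaries.** Section 14-2 sizes the trial so that "a two-sided significance level of 2.5% would result in a sample size of 460 patients (230 patients in each group"), with 90% power for each endpoint. Section 14-3, Analysis of the primary endpoint, repeats the level: "Considering the multiplicity of tests, the two-sided significance level in the comparison between the groups for each endpoint was 2.5" percent, with 97.5% confidence intervals to match.
- **Key secondaries.** Section 14-3 says "the difference in the percentage between the two groups (aspirin-placebo group) and the 95% confidence interval will be calculated". Non-inferiority is concluded when the upper limit is below 10%. The paragraph ends: "Comparisons between the groups for each endpoint will be based on the closed test procedure described above".
- **Other secondaries.** Symptomatic DWI lesions as judged by the investigators, and the 3-month mRS, are each tested at two-sided 5%, with no adjustment or gate.

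The opening of section 14 leaves details to a separate statistical analysis plan. There is no interim analysis.

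**The concern.** The sentence on the closed procedure is the only rule that governs the key secondaries as a family, and it points to text that is not there. What does stand above it is a fixed split of 5% into 2.5% and 2.5%, with no ordering, step-down, gate or passing on of alpha. That split leaves nothing over, yet two further formal conclusions follow, each from a 95% interval.

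These are claims, not descriptions: the protocol treats non-inferiority as demonstrated once the limit is met. One of them concerns bleeding, which the background section names as the worry with antiplatelet drugs in acute rupture. Under the present text, two analysts with the same data could disagree on whether a key secondary may be claimed, for example when only one primary is significant. A procedure chosen after unblinding would carry little weight.

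**Working it through.** **Inputs.** From sections 14-2 and 14-3: 15% against 5% for both primaries, two-sided 2.5% each, 90% power per endpoint, 230 per group; key secondaries by 95% interval, so one-sided 2.5% each. The correlation between the two primaries is not given; 0 to 0.8 is assumed. Power is computed for unstratified tests, whereas the plan uses a stratified CMH test.

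**1. The plan's sample size.** The pooled normal formula for 15% against 5% at two-sided 2.5% and 90% power gives 222 per group, or 241 with continuity correction. Power of Fisher's exact test is 89.9% at 228 per group and 90.2% at 230. The stated 230 is thus reproduced, and the planned power holds (91.2% at 230 by the normal approximation).

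**2. The primaries alone.** Bound: 2 × 2.5% = 5%. If independent: 1 − 0.975² = 4.9%. Controlled.

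**3. All four claims with no gate (worst case).** All four null hypotheses true, tests independent. A two-sided 5% family allows 2.5% in the direction of a claim. There, each primary contributes 1.25% and each key secondary 2.5%:
- four claims: 1 − (0.9875² × 0.975²) = 7.3%; the bound without independence is 2 × 1.25% + 2 × 2.5% = 7.5%;
- the two key secondaries alone: 1 − 0.975² = 4.9%;
- with the primaries counted two-sided: 1 − 0.975⁴ = 9.6% (bound 10%), against 5%.

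**4. Gate on one primary only.** Under the fixed split, one won primary can pass on only its two-sided 2.5%, so a 95% interval is too liberal. Suppose one primary is truly effective and always won, while the other primary and the first key secondary are null and independent. Error in the direction of a claim is 1 − (0.9875 × 0.975) = 3.7% against 2.5%.

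**5. Gate on both primaries, then a fixed order.** Both shares of alpha are released, and 95% intervals are valid. Error over primaries and key secondaries stays at 5%.

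Whether the key secondary decisions are valid thus depends entirely on the gate and the order, which the protocol does not state.

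**6. Holm in place of the fixed split, 230 per group.** By the normal approximation, power is 0.9118 at two-sided 2.5% and 0.9492 at 5%. With independent endpoints:
- per primary: 0.9118 + (0.9492 − 0.9118) × 0.9118 = 94.6%, against 91.2%;
- both primaries: 0.9492² − (0.9492 − 0.9118)² = 90.0%, against 0.9118² = 83.1%.

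Simulation over correlations 0 to 0.8 gives 93.4–94.7% per primary under Holm, and 90.0–91.7% for both, against 83.2–87.2% under the fixed split. Exact enumeration of the uncorrected chi-square test with independent endpoints gives 92.4% rising to 95.6% per primary, and 85.5% rising to 91.7% for both. The two methods agree within about 2.5 points.

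**The case against.** The case on the other side has four parts.

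- **The analysis plan may hold the procedure.** It is not shown here, and section 14 defers detail to it. But the sentence refers to something already described in the protocol. A later document can supply the rule; it cannot make that reference correct. Until it does, the protocol leaves a rule for formal claims empty.
- **A reader might infer that error control fails.** The documents do not show that. The primary family is controlled at 5%, and the sentence itself says that some closed procedure will govern the key secondaries. If it requires both primaries first and then a fixed order, the 95% intervals are sound. The 7.3% belongs to one assumed reading, the ungated one. This objection stands: control is unverified, not shown to be lost.
- **A reader might infer that full two-sided 5% tests are added for the key secondaries.** They are one-sided 2.5% non-inferiority decisions. The two-sided 5% tests are those of the other secondaries, which the protocol does not call key; nominal testing is acceptable there if it is labelled so.
- **A reader might infer that primary power is wasted.** The fixed split is valid, prespecified, matched by its 97.5% intervals and delivers the planned 90%. Holm is a gain in efficiency, not the repair of an error.

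**Conclusion.** The point holds as a defect in the stated rule. The protocol decides two non-inferiority claims by a procedure that it does not contain, after assigning the whole 5% to the primaries. Familywise control over primaries and key secondaries therefore cannot be established from the text.

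The size depends on the rule intended. It is nil if both primaries must be won and the key secondaries are ordered. It is 3.7% against 2.5% in the one-primary case shown. At worst it is about 7.3% against 2.5%, with no gate, all four nulls true and independent tests. The primary conclusions and their planned power are not affected.

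The gain from Holm is a separate, smaller matter: about 2 to 3.5 points per primary and about 4.5 to 7 points for winning both, on the plan's own rates and assumed correlations of 0 to 0.8.

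**What to change.** Before unblinding, replace the sentence on the closed procedure with an explicit one, in section 14-3 and in the analysis plan:

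1. Test the two primaries by Holm: the smaller p-value at two-sided 2.5% and, if it is significant, the other at 5%.
2. Only if both primaries are significant, decide the two key secondaries in a stated fixed order with 95% confidence intervals, stopping at the first that fails.
3. Otherwise report the key secondaries descriptively. Do not decide them with 97.5% intervals after a single primary win: Holm has already handed that alpha to the other primary. In a case like that of step 4 of the working, the error would be 1 − (0.975 × 0.9875) = 3.7% against 2.5%.
4. Label the tests of the other secondaries as nominal.

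The cost is one paragraph and no patients; the sample size stands. There are two drawbacks. Key secondary claims, including the one on bleeding, become conditional on both primaries. And the 97.5% intervals for the primaries no longer correspond exactly to the Holm decisions, which the text should say. If the sponsor prefers to keep the fixed 2.5% split and its matching intervals, steps 2 to 4 still give valid control, without the gain in power.

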**Analysis of secondary endpoints**

1) Incidence of symptomatic ischemic involvement in MRI-DWI (INV).

2) mRS at 3 months

Group comparisons will be performed in the mITT using CMH tests stratified by age (≧65 years, <65 years), sex (men, women), WFNS grade (I-III, IV-V), and modified Fisher grade (0-2, 3-4. The two-sided significance level was set at 5 %. In comparing the groups, mRS is defined as the percentage of patients scoring 2 or less at 3 months. In addition, the number and percentage of patients with events will be calculated for each group, and the difference in the percentage between the two groups (aspirin and placebo groups) and the 95% confidence interval will be calculated. In addition, for the mRS, the number and percentage of patients with an mRS score ranging from 0 to 6 points in the groups were obtained, and the proportional odds model was used to obtain the odds ratio and 95% confidence interval.

**Analysis of exploratory endpoints**

1) Ischemic involvement (number and size) in MRI-DWI

Summary numbers and sizes of individual groups will be calculated for the mITT and compared between groups.

2) Incidence of cerebral hemorrhage along tube tract of ventricular drainage in CT in the first 14 days after surgery.

　　　For mITT, the number and percentage of patients with events will be calculated in each group, and the difference in the percentage between the two groups (aspirin-placebo group) and the 95% confidence interval will be calculated.

**Analysis of safety endpoints**

1) Adverse event rates

2) Incidence of adverse reactions

The numbers and percentages of patients in each group are calculated for SAS.

**Interim analysis**

No interim analysis will be performed in this study.

# **15. Monitoring**

Regular monitoring will be conducted twice a year to ensure that the study is conducted safely and in accordance with the protocol and that the data are accurately collected. Monitoring was based on eCRF-completed data collected in the data center and centrally monitored by the data center, research secretariat, and research representative physicians. Monitoring was not performed during site visits, and reconciliation was conducted with source documents. The data center submits the prepared periodic monitoring report to the research office and the research representative physician. The purpose of periodic monitoring is to increase the scientific ethics of trials by feeding back on problems and is not intended to identify problems in research or institutions. Therefore, research representative physicians review periodic monitoring reports, share problems with researchers at participating institutions, and strive to improve them.

# **16 Ethics**

## **16-1. Declaration of Helsinki and the Clinical Research Act.**

The study will be conducted in compliance with the Declaration of Helsinki (October 2013) and the Clinical Research Act (April 14, 2017).

## **16-2. Consideration for human rights (protection of privacy)**

　　To protect the privacy of research participants, identification codes that do not include elements of personal information are used to identify individual research participants, and even in the publication of research results, information that can identify the identity is protected without publication.

## **16-3. Consideration for safety and disadvantage**

　The aspirin used in this study is off-label for the study population, but it does not suffer any apparent disadvantages compared with daily insurance practice. Although the risk of adverse events arises with treatment, participation in this study does not increase these risks relative to routine practice.

There was no apparent disadvantage to the study participants assigned to the placebo group because they will be treated similarly to the existing treatment. If necessary, the emergency key is opened to confirm the treatment assignment.

Questions related to the study can be consulted at any time, and discontinuation can be offered at any time if the patient does not want to continue the study. In addition, appropriate measures should be taken when adverse reactions that may be related to this study occur, even after the discontinuation or completion of the study.

# **17.** **Cost burden for the study participants**

Because medical care for the research participant under study is within the scope of usual medical care, the medical cost burden of the insurance medical treatment division arises for the research participant. Additionally, the Research Secretariat incurred the cost of the study treatment (aspirin or placebo).

# **18. Health Damage Compensation and Insurance Subscription**

We have clinical research insurance covering this study. For the aspirin used in this study, compensation was provided in the event of an unknown adverse reaction, excluding known adverse reactions specified in the instructions distributed to the research participants.

## **18-1. Compensation for health damage**

◆ The costs for treatment of health hazards at Tokyo Medical and Dental University Hospital and related facilities are to be addressed in accordance with the Principles of Cost Burden in Applications for Voluntary Clinical Research, Unapproved Drugs, which are listed on the Website of the Center for Clinical Trial Management, Tokyo Medical and Dental University Hospital.

## **18-2. Purchase of compensation insurance and liability insurance**

In preparation for compensation and liability, the research investigator and sub-investigator will join the compensation and liability insurance.

# **19. Handling of Personal Information**

To protect the privacy of the research participants, the research participants’ identification codes is used to identify the individual research participants, and their personal information was protected. Even when research results are published, information that can identify the person under study is protected.

Furthermore, the samples and information obtained from this study may be provided to other research institutions after obtaining approval from the Certified Review Board of Tokyo Medical and Dental University, with the protection of the participant’s personal information.

# **20. Storage of records**

　　Person in charge of recordkeeping: [name]

Department of Endovascular Surgery, Tokyo Medical and Dental University Hospital

Location: [name]

Telephone number (direct): [name]

The person responsible for the preservation of records shall retain copies of essential documents and application documents related to the conduct of research, notifications from the director of the hospital, copies of various application forms and reports, copies of research object identification code lists, consent forms, eCRF, and other documents or records required to ensure data reliability. Such documents and records shall be disposed of 10 years after publication of the research.

# **21. Enrollment of study plans and publication of study results**

The outline of the research (name, objective, method, implementation system, selection policy of the participant, etc.) shall be registered in the Clinical Research Protocol and Publication System of Research Outline (jRCT) https://jrct.niph.go.jp prior to its implementation, updated as appropriate according to the changes in the research protocol and the progress of the research, and if the research is completed, the results of the research shall be registered without delay.

The primary results will be presented at international conferences or in English.

# **23. Research funding and conflicts of interest**

　The Certified Review Board confirms that there is no "possible conflict of interest" in the planning, implementation, and reporting of this study that affects the interpretation of the results and results of the study and that the conduct of the study does not compromise the rights and interests of the research participants.

# **24. Changes in the research protocol**

　When necessary, the principal investigator will revise the protocol after obtaining approval from the research coordinating committee. Except for minor cases, in the case of revisions, the Certified Review Board shall undergo a repeat review of the contents of the revisions and the reasons for the revisions, and obtain approval.

